### Measurements

During the study period there are two fixed measurements, at baseline (T0) and after 3 months (T1). At T0 a questionnaire is completed by the athletes, and at both occasions the athletes' jump landing technique is assessed. Additionally, exposure hours and lower extremity injuries are continuously registered during the entire 2010-2011 basketball season (6 months).

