#### Jump landing technique

An improvement in jump-landing technique is determined by registering jump-landing technique of athletes in the CG and IG. Athletes are asked to perform 3 separate maximal vertical jumps which are recorded on camera (SONY HDV 1080i). The researchers collect the jump-landing data at T0 and T1. These jumps are all analyzed through the computer program Darttrainer^®^. In addition, all jumps are evaluated through a predefined list of criteria, the JLS-System (Jump-landing Scorings system) (Table 2). This tool is developed as a field test to evaluate proper jump-landing technique.

**Table 2 T2:** Scorings system Jump-landing Technique (JLS-system)

Front view (observers view)				
***Criteria***	***Description***	***Observation***	***Measurement***	***Score***

Maintaining 'balance' *- Loss of balance*	Lifting one foot or toes of both feet due to falling.	Observe complete jump	Loss of balance present or not	Loss of balance not present or doubt: 0 Loss of balance present: 1
*- Centre of gravity displacement*		At first foot contact: Perpendicular through incisura jugularis	At maximal knee flexion determine the position of incisura jugularis (left/right) compared to perpendicular	Displacement not present or doubt: 0 Displacement left or right: 1

Landing with '*both feet at the same time'*	Not simultaneous: obviously 2 contact times of the feet visible	Observe complete jump	Simultaneous landing present or not	Simultaneous landing present or doubt: 0 Simultaneous landing not present: 1

*'Muscular control' *during landing	Presence of eccentric control during landing, capacity to lower the body in a controlled manner (no side movements of the knee, no sudden stops)	Observe complete jump	Muscular control present or not	Muscular control present or doubt: 0 Muscular control not present: 1

*'Genu varum' - 'Genu valgum' take-off*	Malalignement: valgus or varus position	At maximal knee flexion: perpendicular from SIAS to ankle (middle of malleoli) - Take-off	No varum or valgum: perpendicular goes through centre of patella	Perpendicular through patella or doubt: 0 Patella lateral from the perpendicular: (1 = varum) Patella medial from the perpendicular: (2 = valgum)

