### Statistical analyses

The injury incidence density (IID) is calculated as the number of new injuries per 1,000 hours of participation, using exposure time of each individual participant until the first injury. The number of injuries divided by the total time at risk is the preferred measure of incidence because it can accommodate variations in the exposure time of individuals [34,35]. If an athlete suffers multiple injuries, only the first injury will be considered in the analysis.

Because the unit of allocation was teams, we perform a multilevel Cox proportional hazard regression analysis, using the computer based software SPSS 17.0 (SPSS Inc, Chicago, Illinois, USA), to estimate the hazard ratios (HRs) and 95% confidence intervals (CIs). Teams will be used as cluster levels [36].

The difference between the CG and IG regarding the JLS-system is calculated using Repeated Measures ANOVA (p < 0.05) for normally distributed data and the Mann-Whitney-*U *test (p < 0.05) for data which are not normally distributed.

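### A normality check decides whether a jump-landing (JLS) outcome is compared using its baseline or, on the plain reading, without it, and most JLS items can never meet the check

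*Protocol article*

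**What the plan says.** Under Measurements, technique is recorded at baseline (T0) and three months (T1): "at both occasions the athletes' jump landing technique is assessed". The Jump landing technique section sets the target as improvement: "An improvement in jump-landing technique is determined by registering jump-landing technique of athletes in the CG and IG".

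Table 2 mixes three kinds of item:
- Fault/no-fault codes, for example "Loss of balance not present or doubt: 0 Loss of balance present: 1".
- Two three-level codes for knee alignment, at take-off and at landing, where 0 is aligned and the rest reads "Patella lateral from the perpendicular: (1 = varum) Patella medial from the perpendicular: (2 = valgum)".
- Knee, hip and ankle angles in degrees.

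The Statistical analyses section gives one rule for all of them. The group difference "is calculated using Repeated Measures ANOVA (p < 0.05) for normally distributed data"; the Mann-Whitney U test, at the same threshold, is named "for data which are not normally distributed". The same section uses teams as cluster levels in the Cox model for injuries, but attaches no team term to either JLS test.

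**The concern.** This is a rule that the article states, not a detail it leaves out. The distribution of the data decides more than whether the test is parametric: it decides which comparison is made. With two time points, the ANOVA's group-by-time term compares change between arms. Mann-Whitney is a two-sample test with one value per athlete, and as named it has no place for T0.

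The condition also cannot be met by a single 0/1 or 0/1/2 item, so for those items the second branch is fixed in advance and no categorical method is offered. At stake is the second research question. Baseline data collected in order to measure improvement may go unused for most items, results from the two branches cannot be read side by side, and two items may give answers that reflect their code numbers.

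**Working it through.** The article gives no figure for the JLS analysis, so there is none to reproduce.

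**1. Item count (Table 2).** Front view: 10 items, of which 8 are 0/1 and 2 are 0/1/2. Side view: 3 joints × 2 moments = 6 angles, plus 4 items coded 0/1.

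| Counting | 0/1 | 0/1/2 | Angles | Total | Cannot be normal |
|---|---|---|---|---|---|
| Side view once | 8 + 4 = 12 | 2 | 6 | 20 | 14/20 = 70% |
| Right and left | 8 + 8 = 16 | 2 | 12 | 30 | 18/30 = 60% |

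**2. Is ranking a 0/1 item a problem in itself?** No. With assumed counts of 60/120 v 42/120 faults, Mann-Whitney gives p = 0.0190 and the two-proportion chi-square p = 0.0188. For these items the issue is the T0 value, not the ranks.

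**3. The varum/valgum items.** Assumed counts for aligned/varum/valgum are 48/24/48 in control and 48/48/24 in intervention (120 each).
- Codes 0/1/2: the chance that a control athlete scores higher, plus half the ties, is (0.2×0.4 + 0.4×0.8) + 0.5×(0.16 + 0.08 + 0.08) = 0.56; p = 0.087. The difference favours intervention only because varum ranks below valgum.
- Order varum, aligned, valgum: (0.4×0.4 + 0.4×0.8) + 0.5×(0.08 + 0.16 + 0.08) = 0.64; p = 0.00007.
- Malaligned v aligned: 72 v 72; p = 1.0.
- Valgum yes/no: 0.40 v 0.20, standard error √(0.3×0.7×2/120) = 0.0592, z = 3.38, p ≈ 0.0007.
- Unordered chi-square, 2 df: p = 0.0003.

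The same data give anything from no difference to a very strong one, depending on the coding.

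**4. What T0 is worth for the angles.** Let r be the T0-T1 correlation (assumed; not in the article). Relative variances: T1 alone 1; change, which is the two-time-point group-by-time test, 2(1 − r); T1 adjusted for T0, 1 − r². For a comparison with 80% power on T1 alone, power = Φ(2.802/√v − 1.960), where v is the relative variance.

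| r | v, change | Power | v, adjusted | Power |
|---|---|---|---|---|
| 0.3 | 1.40 | 65.8% | 0.91 | 83.6% |
| 0.5 | 1.00 | 80.0% | 0.75 | 89.9% |
| 0.7 | 0.60 | 95.1% | 0.51 | 97.5% |

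Adjustment cuts variance by 9%, 25% and 49% against T1 alone. Against change the ratio is (1 + r)/2, a cut of 35%, 25% and 15%. The ANOVA branch is itself less precise than T1 alone when r is below 0.5. These formulas are for continuous outcomes and do not carry over to the coded items.

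**5. Number of tests.** Thirty independent tests at 0.05 give 1 − 0.95³⁰ = 0.785, about 79%, for at least one false positive. Positive correlation between items would lower this, so I treat it as a ceiling.

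**The case against.** The strongest reply is that the article does not say Mann-Whitney is run on T1 alone. It could be run on T1 minus T0, and the stress on improvement, with "The researchers collect the jump-landing data at T0 and T1", favours that reading. Both branches would then address change. This stands: loss of T0 is the plain reading of the named test, not something the article states. But the ambiguity is itself the fault, because the two readings are different analyses. Moreover, the change in a 0/1 item takes only the values −1, 0 and 1, so the item still fails the normality condition.

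A reader might infer that most items are ranked on arbitrary codes. The documents do not support that: only 2 of the 14 coded items have more than two levels, and for the other 12 Mann-Whitney is in effect a test of proportions. Even for the two, the order may be deliberate, since the Background names knee valgus as a risk factor. The article does not say so, and the result depends on the coding either way.

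Item-by-item analysis is also an inference. A total is not excluded, though Table 2 defines none and mixes degrees with codes. A reader might likewise take 79% as the trial's false-positive risk, but that needs thirty separate, independent tests, which the article does not state. Nor does naming a test in a condensed article show that estimates with confidence intervals will be missing.

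**Conclusion.** The point holds in a limited form. The rule lets the data's distribution choose between a comparison that uses T0 and one that, as named, does not. With single-item analysis, 70% of items (60% by side) can only reach the second branch. Coding dependence is confined to the two varum/valgum items, where a move from valgum to varum counts as improvement. The precision figures apply only to the angles and rest on an assumed r. Neither named JLS test reflects the team allocation that the Cox model respects. The sample size and the injury analysis are unaffected. The change is worth making, because the data are already collected and the present rule leaves the technique question without a single well-defined answer.

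**What to change.** Drop the normality switch and prespecify the analysis by item type:
- **Angles:** linear mixed model of T1 on arm and T0, with a team effect.
- **0/1 items:** logistic mixed model or GEE of T1 on arm and the T0 item, clustered by team, in line with the Cox model.
- **Varum/valgum:** a predefined dichotomy, malaligned v aligned, analysed as for the 0/1 items, with valgum yes/no reported separately.
- **Multiplicity:** name one key technique outcome in advance and treat the other items as descriptive. If that outcome is to be a summary score, its construction must be written first, because Table 2 gives no rule for combining degrees with codes.

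The cost is analysis wording, slightly more analysis work, and having to commit to the key outcome beforehand. No new data are needed.

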### Implications of this study

This study evaluates the effect of a coach supervised injury prevention program. If successful this will provide valuable information for sports injury prevention practice. As the majority of injuries are sustained in amateur sports where medical guidance is limited, effective coach supervised prevention has a great potential impact on public health.
